## Abstract

**Background:**

Oxygen desaturation during exercise is common in people with chronic obstructive pulmonary disease (COPD). The aim of the study is to determine, in people with COPD who desaturate during exercise, whether supplemental oxygen during an eight-week exercise training program is more effective than medical air (sham intervention) in improving exercise capacity and health-related quality of life both at the completion of training and at six-month follow up.

**Methods/Design:**

This is a multi-centre randomised controlled trial with concealed allocation, blinding of participants, exercise trainers and assessors, and intention-to-treat analysis. 110 people with chronic obstructive pulmonary disease who demonstrate oxygen desaturation lower than 90 % during the six-minute walk test will be recruited from pulmonary rehabilitation programs in seven teaching hospitals in Australia. People with chronic obstructive pulmonary disease on long term oxygen therapy will be excluded. After confirmation of eligibility and baseline assessment, participants will be randomised to receive either supplemental oxygen or medical air during an eight-week supervised treadmill and cycle exercise training program, three times per week for eight weeks, in hospital outpatient settings. Primary outcome measures will be endurance walking capacity assessed by the endurance shuttle walk test and health-related quality of life assessed by the Chronic Respiratory Disease Questionnaire. Secondary outcomes will include peak walking capacity measured by the incremental shuttle walk test, dyspnoea via the Dyspnoea-12 questionnaire and physical activity levels measured over seven days using an activity monitor. All outcomes will be measured at baseline, completion of training and at six-month follow up.

**Discussion:**

Exercise training is an essential component of pulmonary rehabilitation for people with COPD. This study will determine whether supplemental oxygen during exercise training is more effective than medical air in improving exercise capacity and health-related quality of life in people with COPD who desaturate during exercise.

**Trial registration:**

Australian New Zealand Clinical Trials Registry ACTRN12612000395831, 5th Jan,2012

## Background

Pulmonary rehabilitation is an important component of the management of people with chronic obstructive pulmonary disease (COPD) with strong evidence of efficacy [1]. Clinically significant improvements in exercise capacity, symptoms of breathlessness, fatigue and health-related quality of life (HRQoL) are consistently documented in randomised controlled trials of pulmonary rehabilitation [1]. The magnitude of benefit in exercise capacity may be dependent on the intensity of exercise training. In people with COPD, there is some evidence to suggest that training at higher intensities confers greater physiological changes that promote improved exercise capacity [2] and therefore high intensity exercise training is recommended in pulmonary rehabilitation programs [3].

Exercise-induced oxygen desaturation is common among people with COPD, with 47 % of those referred to pulmonary rehabilitation demonstrating a decrease in oxygen saturation to less than 90 % during a six-minute walk test (6MWT) [4]. Exercise-induced desaturation may compromise the intensity of training since those who desaturate often cannot tolerate high intensity exercise [3] and healthcare professionals may strive to minimise exercise-induced desaturation by decreasing training intensity and/or imposing mandatory rests. This reduction in exercise intensity is likely to limit the effectiveness of training [2]. Provision of supplemental oxygen reduces minute ventilation at equivalent work rates in people with COPD and delays the onset of dynamic hyperinflation and the associated dyspnoea [5, 6], thus augmenting exercise capacity in people with moderate to severe COPD [7]. Therefore, supplemental oxygen may enable higher exercise intensity during an exercise training program [8].

For these reasons, supplemental oxygen is often used in pulmonary rehabilitation for people with COPD, especially in those patients who desaturate during exercise [4]. However, evidence to support the use of supplemental oxygen during pulmonary rehabilitation in this patient group is lacking. Since the provision of supplemental oxygen during pulmonary rehabilitation requires trained staff, increases program costs and restricts the locations in which training can be delivered, strong evidence to support or refute the use of supplemental oxygen for those people with COPD who desaturate during exercise is required.

The primary aim of the study is to determine, in people with COPD who desaturate during exercise, whether supplemental oxygen during exercise training is more effective than medical air (sham intervention) in improving endurance exercise capacity and HRQoL, at the completion of exercise training and at six-month follow-up.

The secondary aim is to determine, in people with COPD who desaturate during exercise, whether supplemental oxygen during exercise training is more effective than medical air in improving walking capacity, reducing dyspnoea and increasing levels of daily physical activity, at the completion of pulmonary rehabilitation and at six-month follow-up.

## Methods

### Design

This study will be a prospective, multi-centre, randomised controlled trial with concealed allocation, blinding of participants, therapists and assessors and with intention-to-treat analysis.

### Participants

People will be eligible for inclusion if they have: a diagnosis of COPD (post-bronchodilator forced expiratory volume in one second (FEV_1_) / forced vital capacity (FVC) ratio of <0.7; a greater than 10 pack-year smoking history; medically stable (at least four weeks post an exacerbation); and evidence of oxygen desaturation to less than 90 % during the 6MWT performed on room air. Participants with co-existing cardiac conditions, such as controlled atrial fibrillation and controlled heart failure, will be included to ensure that the sample population is representative and reflective of patients currently referred to pulmonary rehabilitation programs. Informed written consent will be obtained from all participants and the study has been approved by the Ethics Committees of all participating sites (Human Research Ethics Committee of Sydney Local Health District, South Western Sydney Local Health District, Austin Health, The Prince Charles Hospital and Curtin University). The trial is registered with Australian New Zealand Trial Registry: ACTRN12612000395831.

People will be excluded if they are receiving long-term oxygen therapy, have a resting partial pressure of arterial oxygen (PaO_2_) on room air of < 55 mmHg or a partial pressure of arterial carbon dioxide (PaCO_2_) of > 50 mmHg, have participated in any supervised exercise training in the last 12 months or if they have co-morbidities such as severe cardiovascular, neurological or musculoskeletal conditions that are likely to adversely affect performance during assessments or exercise training.

The flow of participants through the trial will reflect the recommendations from the Consolidated Standards of Reporting Trials (CONSORT) guidelines [9] (Fig. 1). Participants will receive written and verbal information explaining the study and written consent will be obtained from each participant. Ethics approval to conduct the study has been obtained from the Ethics Committees of the seven participating sites.

**Fig. 1 Fig1:**
[figure not shown]
Flow of participants through the trial. LTOT = long term oxygen therapy

### Recruitment

Participants will be recruited from referrals to pulmonary rehabilitation programs at the participating sites (Royal Prince Alfred Hospital, Concord Repatriation General Hospital, Liverpool Hospital, Sydney; Austin Hospital and The Alfred Hospital, Melbourne; The Prince Charles Hospital, Queensland; Sir Charles Gairdner Hospital, Perth). Prior to randomisation participants will undergo screening tests to ensure eligibility.

### Screening tests

Participants will perform two 6MWTs while breathing room air to ensure that they meet the study criteria related to oxygen desaturation on exertion. Oxygen saturation (SpO_2_) will be monitored continuously through the 6MWTs via a finger probe attached to a portable saturation monitor (RAD-5v Masimo Corp, Irvine, CA, USA). The nadir SpO_2_ from the better 6MWT (i.e. the greatest distance walked) will be used as the measure of oxygen desaturation.

Additional measures undertaken prior to randomisation (i.e. baseline) will comprise spirometry, resting lung volumes, single breath diffusing capacity for carbon monoxide (D_L_CO) and PaO_2_ and PaCO_2_, whilst breathing room air [10–12].

### Randomisation

Participants who meet the study inclusion criteria and complete the baseline assessments will be randomly allocated into one of the two groups: Oxygen Group or Air Group. Equal numbers of participants will be randomised to each group. Sequence generation will be determined using a computerised random number generator with stratification for study site, six-minute walk distance (6WMD) (≤350 metres vs >350 metres) and level of nadir SpO_2_ from the 6MWT (nadir SpO_2_ between 89-86 % vs < 86 %). Allocation concealment will be achieved by the use of a central telephone randomisation system coordinated through the National Health and Medical Research Council Clinical Trials Centre at The University of Sydney. This will ensure that the researchers are blinded to the sequence generation.

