### Data analysis

For all outcome measures the primary analyses will be via intention-to-treat and will be conducted by a statistician who has not been involved in the study and is unaware of group allocation. Data will be analysed using linear mixed models or analysis of covariance (ANCOVA) if there are between group differences at baseline. Uncertainty regarding the size of the mean between group differences will be quantified with 95 % confidence intervals.

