### Sample size

A total of 110 participants (55 per group) will be recruited to ensure that 88 participants complete the study, allowing for a 20 % loss to follow-up. Regarding primary outcomes, 88 participants will be sufficient to provide 80 % power to detect as significant, at the (two-sided) 5 % level, a minimum 156 second difference [24] in the mean ESWT time between the Oxygen Group and the Air Group. This assumes a standard deviation of 250 seconds for the ESWT, as has been previously reported when comparing two modes of exercise training in COPD [31]. For the HRQoL outcome, 88 participants will be sufficient to provide 80 % power to detect as significant, at the (two-sided) 5 % level, a minimum 10 point difference [32] in the mean CRQ total score between the groups, assuming a standard deviation (SD) of 17 points [33].

Regarding secondary outcomes, 82 participants will be sufficient to provide 80 % power to detect as significant, at the (two-sided) 5 % level, a minimum of 2.5 point difference (a change of 0.5 point per question for a total of five questions in the dyspnoea domain) between groups in the mean score of the dyspnoea domain of the CRQ, assuming a SD of 4.0 [34]. For the physical activity outcome, 82 participants will be sufficient to provide 80 % power to detect as significant, at the (two-sided) 5 % level, a minimum of 1845 step difference in the mean steps per day between the groups, assuming a SD of 2968 steps for people with moderate to severe COPD [35].

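### Randomisation is stratified by site, 6MWD and nadir SpO2, but the analysis does not commit to these factors and ties ANCOVA to observed baseline differences

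*Protocol article*

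**What the plan says.** The Randomisation section of the protocol article describes a sequence generated "with stratification for study site, six-minute walk distance (6WMD"), the distance being split at 350 metres, and a third factor in two bands, "nadir SpO_2_ between 89-86 % vs < 86" %. Allocation is 1:1: "Equal numbers of participants will be randomised to each group". The abstract gives the number of sites, with participants "recruited from pulmonary rehabilitation programs in seven teaching hospitals in Australia". Block size is not given, and no reason is stated for choosing these three factors.

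The Data analysis section describes the model in one sentence: "Data will be analysed using linear mixed models or analysis of covariance (ANCOVA) if there are between group differences at baseline". It lists no covariates and no fixed or random effects. The rest of the section covers intention to treat, an independent blinded statistician and 95% confidence intervals.

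**The concern.** Stratified allocation makes the arms more alike on the stratifying factors than simple randomisation would. If those factors predict outcome, the treatment difference varies less from trial to trial. A model without the factors leaves their variance in the residual, so it reports a standard error larger than the true one. Confidence intervals are then too wide, and the test rejects a true null less often than 5%.

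The article goes further than leaving a covariate list to another document. It states a rule under which ANCOVA is used when the groups are seen to differ at baseline. For 6MWD and nadir SpO2, the design works to prevent that difference. On this rule the factors could be balanced at randomisation and then drop out of the model because they were balanced. At stake is precision on both primary outcomes, ESWT time and Chronic Respiratory Disease Questionnaire (CRQ) total score.

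**Working it through.** **The plan's own figures.** The Sample size section states "A total of 110 participants (55 per group) will be recruited to ensure that 88 participants complete the study, allowing for a 20 % loss", and 88 / (1 - 0.20) = 110 is exact. It then says "88 participants will be sufficient to provide 80 % power to detect as significant, at the (two-sided) 5 % level, a minimum 156 second difference", with an SD of 250 s. This is an unadjusted comparison with 44 per arm:

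- ESWT: SE = 250 x sqrt(2/44) = 53.3 s. 156 / 53.3 = 2.93, and Phi(2.93 - 1.96) gives power of 83.3% (82.5% with the t distribution). The stated 80% is met.
- CRQ total (10 points, SD 17): SE = 17 x sqrt(2/44) = 3.62. 10 / 3.62 = 2.76, which gives 78.8% (77.9% with t). This outcome has no margin.

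**Strata.** 7 sites x 2 x 2 = 28 strata, and 110 / 28 = 3.9 participants per stratum.

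**Upper limit under perfect balance.** If the strata explain a share R2 of outcome variance, the unadjusted SE is too large by 1/sqrt(1 - R2), and the type I error is 2 x [1 - Phi(1.96 / sqrt(1 - R2))]. For R2 = 0.10, 0.20 and 0.30 the ratios are 1.054, 1.118 and 1.195, and the type I errors are 3.9%, 2.8% and 1.9%. With about four participants per stratum, balance is only partial, so these figures exaggerate the conservatism.

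**Simulation with sparse strata.** Assumptions not in the article: R2; permuted blocks of 4; participants spread evenly over sites and categories; half of R2 from 6MWD and a quarter each from nadir SpO2 and site; 22 of the 110 lost at random. ESWT SD is 250 s, with 3,000 trials per setting. The adjusted model has main effects for the three factors. Neither model includes baseline ESWT.

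| Assumed R2 | Unadjusted: reported SE / true SD (s) | Unadjusted type I error | Adjusted SE (s) | Adjusted type I error | Power for 156 s, unadjusted to adjusted |
|---|---|---|---|---|---|
| 0 | 53.2 / about 54 | 5.0% | 54.2 | 4.7% | 82.3% to 80.0% |
| 0.10 | 53.2 / about 52 | 4.3% | 51.4 | 5.1% | 83.4% to 85.6% |
| 0.20 | 53.3 / about 50.5 | 4.0% | 48.5 | 4.9% | 82.6% to 87.8% |
| 0.30 | 53.3 / about 48 | 2.9% | 45.4 | 5.2% | 83.3% to 92.7% |

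A second, separate run gave unadjusted type I errors of 3.9%, 3.1% and 2.6% at R2 = 0.10, 0.20 and 0.30. Adjusted SEs were 51.4, 48.4 and 45.4 s. Power was 85%, 88-89% and 92% adjusted, against 84-85% unadjusted. With 3,000 trials the simulation error near 5% is sqrt(0.05 x 0.95 / 3000) = 0.4 percentage points, so the type I errors are best read as ranges.

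Relative to the adjusted analysis, unadjusted intervals are about 4%, 10% and 17% wider (53.3 / 51.4, 53.3 / 48.5 and 53.3 / 45.4).

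**CRQ total.** Only the ideal formula was applied here. At R2 = 0.10, power would rise from 77.9% to 82.0% (t).

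**The case against.** The strongest reply is that silence is not exclusion. The article condenses a fuller plan, covariate lists are commonly left to the SAP, and a linear mixed model could carry site, 6MWD and nadir SpO2. This stands against one tempting inference, that the stated analysis leaves the factors out. The text neither includes nor excludes them. It does not remove the point about the conditional ANCOVA rule, which the article itself states.

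The condition can also be read as concerning baseline imbalance in general, perhaps in the outcomes themselves. Balancing 6MWD and nadir SpO2 need not prevent a chance difference in baseline ESWT or CRQ. That is fair. The claim is only that imbalance in the stratifying factors is less likely, and that adjustment should not wait for imbalance of any kind.

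A reader might also infer that precision is certain to be lost. The article does not support that. It gives no R2 and does not say that the factors were chosen as prognostic. The Primary outcomes section sets ESWT speed from each participant's own peak and aims for a baseline time of five to ten minutes, which may weaken the link between 6MWD and ESWT time (an inference). If R2 is zero, adjustment costs slightly more than it gains.

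Finally, any error is on the safe side. Omission brings neither bias nor excess false positives. Because the trial was sized on an unadjusted comparison, the loss is a gain forgone and not a shortfall against the planned ESWT power. This stands and limits the weight of the point.

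**Conclusion.** The point holds in a limited form. The article randomises on three factors, does not commit to analysing them, and makes ANCOVA depend on an observed baseline difference that stratification makes less likely for those factors. If the factors predict outcome and are omitted, the analysis is conservative. Over an assumed R2 of 0.10 to 0.30, the type I error is roughly 4% falling to 2.5-3%, and an ESWT SE of 53.3 s could be 51.4 to 45.4 s. At R2 = 0 there is nothing to gain and about 1 s to lose.

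The direction is secure whenever the factors are prognostic. The size rests on the assumed R2, blocks of 4, even strata and random loss, and part of the gain would come from adjusting for the baseline outcome anyway. The matter should be corrected, but it does not threaten the validity of the trial.

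**What to change.** Replace the conditional sentence in the Data analysis section with one prespecified model for every primary and secondary outcome. It should include the outcome's baseline value, 6MWD, nadir SpO2 and site (fixed or random), and state that these terms stay in whatever baseline differences are seen. Enter them as main effects. With about 3.9 participants per stratum, 28 separate stratum terms should not be fitted. Whether 6MWD and nadir SpO2 enter as continuous values or as their two bands can be settled in the SAP, provided it is fixed in advance.

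The cost is wording and about eight degrees of freedom (1 for 6MWD, 1 for nadir SpO2, 6 for seven fixed sites), which takes the residual from 86 to 78 with 88 analysed. The baseline outcome takes one more. No new data are needed, since site, 6MWD and nadir SpO2 are known before randomisation and the outcomes are measured at baseline.

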### Blinding

Participants, exercise trainers and assessors will be blinded as to whether the participants are receiving oxygen or medical air. Oxygen concentrators (Air Liquide, Healthcare Pty Ltd, Australia) will be used for the delivery of supplemental oxygen to the Oxygen Group. Oxygen concentrators modified by Air Liquide with Therapeutic Goods Administration (TGA) approval to deliver medical air only, will be used for the Air Group. The concentrators for the Oxygen and Air Groups will be identical and coded by an independent body (Air Liquide, Healthcare Pty Ltd, Australia). The code to distinguish which intervention a participant is receiving will only be available to the randomisation centre.

### Experimental intervention

Both the Oxygen and Air Groups will participate in the same supervised exercise training program. The Oxygen Group will receive intranasal oxygen at 5 L/min from an oxygen concentrator during this exercise training program. The Air Group will receive intranasal air at 5 L/min from an oxygen concentrator modified to deliver air during this exercise training program. The fixed flow rate of 5 L/min will ensure adequate delivery of gas through the concentrators for both groups.

### Exercise training

Exercise training will consist of supervised treadmill walking and stationary cycling, performed three times per week for eight weeks. The training period will be extended to 10 weeks if training is interrupted by the inability to attend due to illness with the aim of completing a minimum of 20 sessions. The initial duration of exercise training will be 30 minutes (20 minutes treadmill walking and 10 minutes stationary cycling) and will be progressed up to a total of 40 minutes (20 minutes treadmill walking and 20 minutes stationary cycling) by week three.

The initial exercise intensity for each mode of training will be standardised across the Oxygen and Air Group. For the treadmill walking, the initial intensity will be set at 80 % of the participant’s average speed achieved during the 6MWT (based on the best 6MWT performed at the screening assessment). For stationary cycling, the initial intensity will be set at 60 % of the peak work rate estimated using the distance walked in the best 6MWT [13].

#### Progression of training

Participants will score dyspnoea and rate of perceived exertion (RPE) after each treadmill and cycle training session using the modified dyspnoea and RPE 0–10 scales [14, 15]. These scores will be used to guide the progression of both treadmill and cycle training, with the aim to keep either dyspnoea or RPE at a ‘moderate’ to ‘somewhat severe’ level (i.e. a score of 3 to 4).

To progress treadmill training, the walking speed will be increased once a participant completes three sessions at the prescribed speed. If the initial walking speed is < 3 km/hr, the speed will be increased by 0.25 km/hr. If the initial walking speed is >3 km/hr the speed will be increased by 0.5 km/hr. If the participant reports both dyspnoea and RPE scores < 3 after a treadmill training session, the speed for the next training session will be increased as tolerated. Once the participant has reached a walking speed of 5 km/hr, the speed will be reduced to 4.5 km/hr and a gradient of 1 to 2 % will be added. The gradient will be increased by 1 to 2 % after every three training sessions if symptoms of dyspnoea and RPE allow (i.e. dyspnoea and RPE scores < 3). If the participant experiences difficulty achieving a walking speed of 5 km/hr (e.g. unable to walk fast due to short stride length) and reports dyspnoea or RPE scores < 3, the gradient will be introduced earlier to ensure the exercise intensity is appropriate.

Cycle training will be progressed after six sessions if the participant reports dyspnoea or RPE scores < 3.The progression will be an increase in duration of cycle training by five minutes, to a maximum of 20 minutes. Once the participant is able to successfully perform three sessions of cycle training for 20 minutes and if dyspnoea and RPE scores are < 3, the work rate will be increased by 5 watts. Thereafter, for the remainder of the training program, the intensity of the cycle based training will be increased in 5 watt increments, once a participant completes three sessions at the prescribed intensity with dyspnoea and RPE scores <3.

